## Abstract

**Background:**

Lifestyle changes can protect or improve brain health in older adults. However, sustained lifestyle change is difficult for everyone and may be more difficult for those with executive dysfunction, including some people living with HIV. Thus, the key question is how we can improve adherence to the most promising interventions among people living with HIV experiencing cognitive difficulties. Goal management training is a cognitive rehabilitation program that targets executive dysfunction by teaching goal-directed behaviour and self-management. It is a promising means to improve adherence to lifestyle interventions.

**Objective:**

To estimate the extent to which goal management training before a healthy lifestyle program is associated with greater adherence to health recommendations, achievement of health-related goals, and better brain health and health outcomes compared to the healthy lifestyle program alone among people living with HIV.

**Methods:**

Brain Health Now cohort participants with cognitive difficulties or are not aging successfully are eligible. All participants will be given health resources, a health coach, a goal-setting digital application, and access to an online goal-setting workshop. The intervention group will participate in nine 2-h goal management training sessions and then will enter the healthy lifestyle program. Control participants will enter the healthy lifestyle program directly. A total sample of 100 participants will participate for 12 months. The main outcome is adherence to the healthy lifestyle program, defined as the number of weeks where physical activity adherence targets were met (150 min per week, measured with an activity monitor). Weekly social activities will be captured via self-report with confidential photo validation. We will send weekly health state reports to the participants. Downstream outcomes include cognitive ability, health-related quality of life, mobility, vascular risk profile, and social network size. We will analyze the data using a linear regression model.

**Discussion:**

This project is the first to test whether goal management training can augment adherence to health recommendations among individuals with cognitive difficulties. If successful, behavioural interventions such as goal management training could be implemented as an adjunct to lifestyle interventions in other clinical populations.

*Trial registration:* This trial was registered on clinicaltrials.gov (NCT04345484) on April 14, 2020, https://clinicaltrials.gov/ct2/show/NCT04345484?term=NCT04345484&draw=2&rank=1.

## Background

### Successful aging with HIV

Successful aging has become a priority among people living with HIV as they live longer with this chronic condition. There are three proposed components of successful aging: high cognitive and physical functioning, low levels of disease and disability, and active engagement in life [1]. It is estimated that 30–60% of people living with HIV experience cognitive difficulties [2–4]; however, these estimates are susceptible to selection bias and may overestimate the prevalence of cognitive difficulties [5]. Given the proportion of people living with HIV with poor brain health, strategies are needed to help these individuals age successfully.

### Lifestyle interventions

High quality evidence from HIV-negative individuals shows that healthy lifestyle changes including physical activity [6–11], diet [12], social activity [13], and cognitive training [14] can protect or improve brain health. There is also evidence that lifestyle change can improve cognitive ability in people living with HIV [15–20]. A cross-sectional study of 139 people living with HIV determined that an increasing number of active lifestyle factors (physical activity, social activity, and employment) was associated with 41% lower prevalence of HIV-associated neurocognitive impairment [17]. Furthermore, the investigators determined that each of the lifestyle factors (physical activity, Cohen’s d = 0.58; social activity, Cohen’s d = 0.41; employment, Cohen’s d = 0.57) was associated with better cognition.

Despite the evidence that lifestyle factors are associated with better cognitive ability, only 51% of people living with HIV are meeting the World Health Organization physical activity recommendations, compared to 65% of HIV-negative individuals [21]. Relative to other chronic conditions, people living with HIV are among the most physically inactive, taking only 5899 steps per day on average, according to a meta-analysis of 24 studies [22]. Three meta-analyses [23–25] have reported variable adherence (61–100%) and high withdrawal rates (20–29%) among people living with HIV who participate in aerobic and resistance exercise trials. Sustained lifestyle change is difficult for everyone, but may be harder for those with executive dysfunction, including many people living with HIV [26]. Thus, the key question is how we can improve adherence to the most promising interventions in people living with HIV experiencing cognitive difficulties.

Goal management training (GMT) has become a recommended cognitive rehabilitation strategy to improve executive function among older adults [27]. GMT is a standardized program delivered over 9 weeks in small groups that targets executive dysfunction by teaching goal-directed behaviour, self-management, and mindfulness [28]. GMT also trains participants to use explicit strategies to reduce cognitive load in everyday tasks, and methods to cue attention to maintain focus on specific tasks, through weekly 2 h sessions and home practice. A systematic review and meta-analysis of 15 studies determined that GMT had a small to moderate effect on executive function immediately following the intervention (Hedges’ *g* = 0.227) and at follow-up (Hedges’ *g* = 0.549) among healthy individuals and those with conditions affecting cognitive performance [27].

GMT has been tested very little among people living with HIV. A study of 90 people living with HIV who were randomized to a single session of GMT, GMT plus metacognitive training, or control (education and origami task) found moderate effects of the combined GMT groups on everyday multitasking performance and metacognitive tasks compared to controls [29]. GMT has not been used to augment goal-directed lifestyle changes among people living with HIV.

This study will test an innovative approach to enhance adherence to lifestyle interventions, building on feasibility evidence from pilot trials in the Brain Health Now cohort study, where we have tested three brain-health-promoting interventions, including computerized cognitive training, GMT, and exercise. Feasibility was demonstrated for both GMT and exercise, based on the success of recruitment and retention, improvements in brain health outcomes, and participant feedback [30, 31]. The varied adherence observed in these pilot trials suggests that people living with HIV who have cognitive difficulties may need more assistance to make and sustain behaviour changes. While GMT was developed to improve goal-directed behaviour in general, we recognized that this cognitive rehabilitation approach could be applied to improve the ability to achieve health-promoting lifestyle goals in particular. We therefore hypothesize that GMT priming before a personalized healthy lifestyle program (HLP) will improve adherence to the program and subsequently improve health outcomes, compared to the HLP without GMT priming in people living with HIV experiencing cognitive difficulties.

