*Set*: One of the short video modules will include instruction on specific, measurable, attainable, relevant, and time-bound (SMART) goals and demonstration of the goal-setting app to use for recording and monitoring goals. The app will guide all the participants through the steps to write and follow up on their SMART goals. Participants will be encouraged to be as specific as possible when filling in a box on the app with an aspect of their health that they wish to improve. The goal-setting app will give them feedback on their goals through simplified Goal Attainment Scaling [40]. Participants will have the option to contact other participants with similar goals via their health coach. For example, if multiple participants have goals related to yoga, the coach can suggest they communicate and help each other achieve their goals, as long as the participants have consented to this option.

*Go*: Following the workshop, the participants will be randomized. Randomization will be done in a 1:1 ratio by the study statistician using randomization.com. Stratification by language will be carried out, as GMT will be done in either French of English. The intervention group will participate in GMT for 9 weeks and then will enter the HLP for 43 weeks. Control participants will enter the HLP directly and will participate for 52 weeks. It is not possible to blind participants in this type of study.

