### Goal management training

The intervention group will participate in GMT, a standardized cognitive rehabilitation program, which will be provided per the manual. It consists of 9 online sessions, once per week, for two hours [41]. Participants will be given homework to complete between the sessions. There are five steps in GMT [28]. In stage 1, participants are asked to stop and ask what task they are trying to accomplish. They select their goals in stage 2, and these goals are partitioned into smaller steps in stage 3. Stage 4 involves encoding and retention of goals and steps. In stage 5, participants monitor their outcomes to make sure they align with their original goals [28].

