### Statistical analysis

The analysis assumes that the distribution of physical activity-weeks at the end of the study period will be near normal, permitting a linear regression model; if not, a Poisson model can be used. Both intention-to-treat, with imputation and sensitivity analyses, and per protocol analyses will be conducted. Intention-to-treat will address the benefit of offering GMT as a service to all with need, while the per protocol analysis will address the benefit to those who are able to adhere to the program and will help identify characteristics (including sex and gender) of those most able to benefit. We will follow the Sex and Gender Equity in Research (SAGER) [66] guidelines and will present study data disaggregated by sex and gender. To address bias resulting from missing data, we will conduct multiple imputation on the data for outcomes with sufficient data [67].

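### GMT is very likely given in small groups in one arm only, but the planned regression and the sample size make no allowance for correlation within those groups

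*Protocol article*

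**What the plan says.** The Background (under Lifestyle interventions) describes the intervention in general: "GMT is a standardized program delivered over 9 weeks in small groups". The Methods section Goal management training calls it "a standardized cognitive rehabilitation program, which will be provided per the manual" and adds "It consists of 9 online sessions, once per week, for two hours". It does not repeat the group format and gives no group size or number of groups.

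The Go paragraph of the Intervention section says "Stratification by language will be carried out, as GMT will be done in either French of English". It assigns GMT to the intervention arm only; for the other arm, "Control participants will enter the HLP directly and will participate for 52 weeks". Allocation is 1:1.

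The Statistical analysis section assumes a near-normal count of activity-weeks, "permitting a linear regression model; if not, a Poisson model can be used". The Abstract also names linear regression, and Sample size mentions ordinal regression as a further fallback. None of these is described with a term for GMT group. Sample size uses a difference of 9 weeks, an SD of 11 weeks and a 15% inflation for dropout and imputation. It arrives at 38 per group for 90% power and then targets 50 per group, to cover uncertain assumptions and incomplete data. Neither allowance is attributed to clustering.

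**The concern.** Members of one GMT group would spend 9 × 2 = 18 hours together on goal-setting and self-management, the mechanism through which the trial expects to change activity. They would probably also share a facilitator and a calendar start, and so a season. Their counts of activity-weeks may therefore resemble each other more than those of participants in different groups. Controls have no such grouping, so any such correlation adds variance to the intervention mean only.

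A regression that treats all 100 participants as independent would miss that variance. Confidence intervals would be too narrow and the confirmatory tests would reject a true null more often than 5% of the time. This applies to both primary outcomes, physical activity-weeks and social activity-weeks. The sample size calculation makes the same assumption of independence.

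**Working it through.** **Is the trial partially nested?** Four statements are read together:
- the Background defines GMT as a small-group program;
- the Methods deliver it by its manual in weekly sessions;
- randomization is stratified by language because of the language in which GMT is run, which fits shared sessions;
- only one arm receives it.

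Nothing in the article points to individual delivery. Group delivery in this trial is thus a strong inference, not an explicit Methods statement.

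**The plan's own figure.** Inputs from Sample size: difference 9, SD 11, inflation 15%, power 90%, alpha 0.05 (taken as two-sided).
- Inflating the SD: 11 × 1.15 = 12.65, and 9/12.65 = 0.711, which matches the stated 0.71. Then n = 2 × (1.960 + 1.282)²/0.711² = 41.5, so 42 per arm (43 with the t distribution), not 38.
- Inflating the variance: 11 × √1.15 = 11.80, d = 9/11.80 = 0.763, and n = 37 (38 with the t distribution). This matches 38 but not 0.71.

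The stated effect size and the stated 38 do not come from the same reading. That is a separate matter to reconcile. What counts here is that both readings use a formula for independent observations, with no design effect. Power is given below for both.

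**Adding clustering in one arm.** Assumed, because the article gives neither: group size m = 6 or 8, ICC 0.01 to 0.10. With n = 50 per arm:
- design effect in the GMT arm: DE = 1 + (m − 1) × ICC;
- true variance of the difference relative to the ordinary one: R = (1 + DE)/2;
- factor by which the true standard error exceeds the ordinary one: √R;
- actual type I error of the ordinary test: 2 × [1 − Φ(1.96/√R)];
- power: two-sided t test, 50 per arm, effect size d/√R.

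Example with m = 8 and ICC 0.05: DE = 1 + 7 × 0.05 = 1.35; R = 2.35/2 = 1.175; √R = 1.084; 1.96/1.084 = 1.808; type I error = 7.1%.

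| m | ICC | DE | R | √R | Type I error | Power, d = 0.71 | Power, d = 0.763 |
|---|---|---|---|---|---|---|---|
| any | 0 | 1.00 | 1.000 | 1.000 | 5.0% | 94% | 97% |
| 6 | 0.01 | 1.05 | 1.025 | 1.012 | 5.3% | 94% | 96% |
| 6 | 0.02 | 1.10 | 1.050 | 1.025 | 5.6% | 93% | 96% |
| 6 | 0.05 | 1.25 | 1.125 | 1.061 | 6.5% | 91% | 95% |
| 6 | 0.10 | 1.50 | 1.250 | 1.118 | 8.0% | 88% | 92% |
| 8 | 0.01 | 1.07 | 1.035 | 1.017 | 5.4% | 93% | 96% |
| 8 | 0.02 | 1.14 | 1.070 | 1.034 | 5.8% | 93% | 95% |
| 8 | 0.05 | 1.35 | 1.175 | 1.084 | 7.1% | 90% | 94% |
| 8 | 0.10 | 1.70 | 1.350 | 1.162 | 9.2% | 86% | 90% |

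A simulation of the ordinary t test, with the 50 GMT participants split into groups of about 6 or about 8 (100,000 trials per row), agrees with the type I column to within about 0.2 of a percentage point. The power columns assume 50 analysed per arm and 98 degrees of freedom. A model with the smaller degrees of freedom appropriate to few groups would give slightly less.

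**The case against.** The strongest reply has four parts.

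*Group delivery is inferred.* The explicit sentence is Background text, and the Methods give no group size, number of groups or facilitator. This stands, and the point is worded accordingly. But the Methods tie delivery to the manual, and no passage suggests one-to-one sessions.

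*The ICC may be small.* The physical activity outcome is tracked person by person, mostly after GMT has ended, in a largely home-based program with weekly coaching. An ICC of 0.01–0.02 is as compatible with the article as 0.05–0.10, and the effect is then minor. This stands too. A reader might infer that the standard errors are certainly too small; the article supports only that they are too small if the ICC exceeds zero.

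*The model sentence comes from a condensed article.* It neither excludes a group effect nor specifies a variance estimator, and an analysis plan that is not shown could add one. So the article does not show that clustering will be ignored. The firmer evidence is the sample size, a finished calculation whose stated allowances are for other things.

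*Dependence may not be confined to GMT groups.* Health coaches serve both arms and may put participants with similar goals in touch with each other. A group effect in the GMT arm alone would not capture that, and with few groups its variance will be poorly estimated. Both are fair limits on the remedy, but neither removes the one-sided grouping.

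**Conclusion.** The point holds as a conditional one. The trial is very likely partially nested, and neither the named analysis nor the sample size makes any allowance for it. With assumed groups of 6–8 and 50 per arm, the ordinary standard error is too small by a factor of 1.01 to 1.16 for ICC 0.01–0.10. Type I error is then about 5.3–9%, and a nominal 95% interval covers about 95% down to 91%. At ICC zero there is no effect.

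A reader might also infer that the trial is underpowered. The documents do not support that. The target of 50 per arm, although set for other reasons, absorbs much of the loss. Power is about 86–94% at an effect size of 0.71, and 90–96% on the reading that reproduces 38 per group. The harm that matters is to the error rate and interval width of the confirmatory comparisons, and it is moderate and cheap to prevent.

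**What to change.** - State in the Methods whether GMT is given in groups, with the planned group size and number of groups. Record each participant's GMT group. The Design section says the trial is ongoing, and membership may be hard to reconstruct later.
- Analyse the primary outcomes with a partially nested model: a random intercept for GMT group in the intervention arm only, separate residual variances by arm, and Satterthwaite or Kenward-Roger degrees of freedom. Include language, the randomization stratum, as a fixed effect. If the Poisson or ordinal fallback is used, it needs an equivalent allowance for group.
- State power at 50 per arm over a range of assumed ICCs, including small values.

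Cost: slightly wider confidence intervals, and a group variance estimated from only about 6 to 9 groups (50/8 ≈ 6; 50/6 ≈ 8), hence imprecisely. No extra participants and no change to the intervention.

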### Study objectives

The overall objective of Action for Brain Health Now is to understand, empower, and act to protect and improve brain health in HIV, and equip patients to take charge of their brain health. This sub-study is directed to the third aim, act. This proposed study addresses the real-world challenge of implementing tailored recommendations, recognizing that individuals with cognitive difficulties who would benefit the most from lifestyle changes are less equipped to successfully adopt and sustain healthy behaviours. We will trial a novel cognitive rehabilitation approach using GMT to boost adherence to a tailored active living intervention.

### Specific objective

To estimate the extent to which goal management training before a personalized healthy lifestyle program is associated with greater uptake of health recommendations, achievement of health-related goals, and better brain health and general health outcomes compared to the healthy lifestyle program alone.

## Methods

### Design

This is a single-blind, language stratified, parallel group randomized controlled trial. This trial was registered on clinicaltrials.gov (NCT04345484). This protocol is informed by the Standard Protocol Items: Recommendations for Interventional Trials (SPIRIT) checklist. This study is ongoing.

### Population

This is a sub-study of the Action for Brain Health Now (ABHN) cohort (http://brainhealthnow.mcgill.ca), which consists of 840 people living with HIV [32–34]. The extension for ABHN will involve 4 yearly visits for all participants. This will provide longitudinal data on the evolution of brain health trajectories in HIV over a minimum of 3 years. More than 20% of the cohort will be over 70 by the end of this study.

Any member of the ABHN from four existing sites (Special Immunology Services Clinic in Hamilton, Maple Leaf Clinic in Toronto, Clinique Médicale l’Actuel in Montreal and the McGill University Health Centre in Montreal) who is willing to undertake the intervention activities is eligible for the trial, provided they: Have one or more indicators of cognitive difficulties [35], defined here as a Brief Cognitive Ability Measure (B-CAM) [36] score or Communicating Cognitive Concerns Questionnaire (C3Q) [37] score (or both) below cohort median values (56/100 for B-CAM, 27/36 for C3Q) or do not meet successful aging criteria, with successful aging defined as meeting or exceeding Canadian norms on 7 or more of 8 health-related quality of life domains on the RAND-36 [38]. Participants will be excluded if they previously participated in GMT.

For new participants entering the cohort, the eligibility criteria are: Age ≥ 45; HIV + for at least 1 year; ability to communicate adequately in either French or English; and ability to give written informed consent. The exclusion criteria for new participants are as follows: Dementia (Memorial Sloan Kettering-rating stage 3 or more on the cognitive component only); life expectancy less than 3 years or other personal factor limiting the ability to participate in follow-up; non-HIV-related neurological disorder likely to affect cognition; known active central nervous system opportunistic infection or hepatitis C requiring interferon treatment during the follow-up period; known psychotic disorder; current substance dependence or abuse within the past 12 months; or previous participation in GMT.

### Recruitment

Our team will do a search among our cohort participants and create a list of potential participants. If these potential participants have agreed in the main study consent form to be contacted for sub-studies, they will get a phone call, email, or will be recruited during their regular study visit by the research coordinator involved in the main study. If cohort participants decline to participate in this sub-study, we will ask them their reasons for declining [5]. Those who agree to participate in the study will sign the consent form provided by the research coordinator. We have received conditional approval from the McGill University Health Centre Research Ethics Board (ABHN_Goals 2020-6202).

### Intervention

The flow of participants through the intervention trial is shown in Fig. 1.

**Fig. 1 Fig1:**
[figure not shown]
Participant flow diagram

*Ready*: All study procedures will occur online. All cohort participants will receive a personalized *My Personal Brain Health Dashboard* populated directly from their study data, which provides them with information on 15 areas including cognitive ability, health outcomes, health-related quality of life, and lifestyle factors. Participants also receive a document with *7 Simple Tips for Better Brain Health*. In addition, the participants of this trial will receive a list of relevant local resources (e.g., community activities and groups, online exercise classes, smoking cessation programs). We offer this to the cohort participants, as it represents current best practices for health promotion: personalized risk assessment, tailored recommendations, and concrete suggestions for action [39]. However, this generic approach may not address the needs of those with brain health challenges.

All of the participants who agree to enter the trial will be invited to attend the online Ready, Set Workshop which will occur before randomization and will last approximately four hours. As part of the workshop, all of the participants will be shown via pre-recorded videos how to interpret the *My Personal Brain Health Dashboard*, use their activity tracker, and use two digital applications (a goal-setting app and the MyHealth app). Participants will be sent the Garmin vívofit 4 Activity Tracker via Canada Post. Participants who do not have an app compatible device such as a smartphone or tablet will be provided with a smartphone for the duration of the study.

*Set*: One of the short video modules will include instruction on specific, measurable, attainable, relevant, and time-bound (SMART) goals and demonstration of the goal-setting app to use for recording and monitoring goals. The app will guide all the participants through the steps to write and follow up on their SMART goals. Participants will be encouraged to be as specific as possible when filling in a box on the app with an aspect of their health that they wish to improve. The goal-setting app will give them feedback on their goals through simplified Goal Attainment Scaling [40]. Participants will have the option to contact other participants with similar goals via their health coach. For example, if multiple participants have goals related to yoga, the coach can suggest they communicate and help each other achieve their goals, as long as the participants have consented to this option.

*Go*: Following the workshop, the participants will be randomized. Randomization will be done in a 1:1 ratio by the study statistician using randomization.com. Stratification by language will be carried out, as GMT will be done in either French of English. The intervention group will participate in GMT for 9 weeks and then will enter the HLP for 43 weeks. Control participants will enter the HLP directly and will participate for 52 weeks. It is not possible to blind participants in this type of study.

